### Outcomes {12}

The primary endpoint of this trial is the difference in driving pressure (ΔP) between the intervention and control group during general anesthesia in endotracheal intubation and volume-controlled ventilation (VCV). Secondary endpoints include:

Mechanical Power of ventilation (elastic-dynamic, tidal and total).Compliance of the respiratory system.Intraoperative fluid requirements.Average intraoperative vasopressor requirements (µg/kg/min).Number of intraoperative hypotension events (MAD < 65 mmHg for > 1 min).Time-weighted average of hypotension.Number of alveolar recruitment maneuvers (to be performed if SpO_2_ < 90% with FiO_2_ > 60%).SpO_2_ after arrival in recovery room (without oxygen insufflation).Number of patients with indication for oxygen insufflation (to maintain SpO_2_ ≥ 90%).Change in lung aeration score between before surgery and after arrival in recovery room(determined by lung ultrasound).Overall postoperative pulmonary complications.

For further clarification see, Table 1 (“Outcome Definition”).

**Table 1 Tab1:** Outcome definition

**Domain**	Respiratory mechanics	Rescue therapy	Hemodynamics	Postoperative status
Specific measures	• Driving pressure • Mechanical power of ventilation (elastic-dynamic, tidal, and total) • Compliance of respiratory system	• Number of alveolar recruitment maneuvers	• Intraoperative fluid requirements • Average intraoperative vasopressor requirements • Number of intraoperative hypotension events • time-weighted average of hypotension	• SpO_2_ after arrival in recovery room • Number of patients with additional oxygen insufflation^a^ • Change in lung aeration score
Specific metric	Difference between control and intervention group	Difference between control and intervention group	Difference between control and intervention group	Difference between control and intervention group
Method of aggregation	Mean + SD (parametric data) or Median/IQR (non-parametric data)	Mean + SD (parametric data) or Median/IQR (non-parametric data)	Mean + SD (parametric data) or Median/IQR (non-parametric data)	Mean + SD (parametric data) or Median/IQR (non-parametric data) and four-square table^a^
Time point	Intraoperative	Intraoperative	Intraoperative	Postoperative

Outcomes are defined following the framework of Saldanha et al. [20]

^a^Four-square table is only used as method of aggregation for “number of patients with additional oxygen insufflation”

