## Statistical methods

### Statistical methods for primary and secondary outcomes {20a}

The primary objective of the study is to determine whether BMI-adjusted ventilation strategies result in a reduction of driving pressure. Data are tested for normal distribution using the Shapiro–Wilk test. Differences between the intervention group and the control group are assessed with a two-tailed unpaired *t*-test for normally distributed continuous data and with the Mann–Whitney test for non-normally distributed continuous data. In addition, descriptive statistical analyses (mean ± standard deviation, median, interquartile range, and 95% confidence interval, if applicable) will be performed.

For secondary endpoints, to evaluate the changes in lung ultrasound score between the pre- and postoperative groups and between the intervention groups, a two-way ANOVA will be performed with the time point (preoperative/postoperative) as one independent variable and the study group (intervention/control) as the other independent variable. For categorical variables (hypotension events, number of patients requiring supplemental oxygen), Fisher’s exact test will be used. For the secondary endpoint “time-weighted average of hypotension events,” the area under the threshold of 65 mmHg (AUC) for each event will be calculated by summing the difference between MAP and the threshold, multiplied by the duration of the event. Total AUC will be divided by the observed time, which varies by patient. This results in a time-weighted average of hypotension per patient.

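### The number of intraoperative hypotension events is a per-patient count in Outcomes {12} and Table 1, but the statistical methods call it categorical and assign Fisher's exact test

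*Protocol article*

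**What the plan says.** Three places in the protocol article bear on this endpoint.

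- **Outcomes {12}, list of secondary endpoints:** "Number of intraoperative hypotension events (MAD < 65 mmHg for > 1 min"). One patient can have several events.
- **Outcomes {12}, Table 1:** the endpoint stands in the hemodynamics column, whose method of aggregation is "Mean + SD (parametric data) or Median/IQR (non-parametric data"). The table's footnote reads "Four-square table is only used as method of aggregation for" the number of patients with additional oxygen insufflation.
- **Statistical methods {20a}:** "For categorical variables (hypotension events, number of patients requiring supplemental oxygen") Fisher's exact test is to be used.

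The same section gives a rule for numeric data: a t-test if normally distributed, otherwise a comparison "with the Mann–Whitney test for non-normally distributed continuous data". For the separate endpoint of time-weighted average hypotension it adds: "Total AUC will be divided by the observed time, which varies by patient".

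**The concern.** Fisher's exact test needs a contingency table of patients by category. The document defines no category for hypotension, such as patients with at least one event, and Table 1 rules out the four-square table for this endpoint. Whoever runs the analysis must then either invent a categorisation or depart from the stated test, possibly with the data in view.

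The obvious categorisation, any event or none, loses information. A patient with one event in 5 hours (0.2 per hour) and a patient with four events in 2 hours (2 per hour) both count as one yes. Observation time matters because eligibility sets only a minimum expected duration of surgery (over 2 h), and {20a} itself notes that observed time differs between patients.

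Hypotension is among the harms listed under Adverse event reporting {22}, and the Discussion says the study will evaluate safety. A comparison with needlessly low power could therefore be read as reassurance.

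**Working it through.** **1. The statements side by side**

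| Item | Hypotension events | Patients needing oxygen |
|---|---|---|
| Unit in Outcomes {12} | events per patient | patients |
| Aggregation in Table 1 | mean/SD or median/IQR | four-square table |
| Test in {20a} | Fisher's exact | Fisher's exact |

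The oxygen column is consistent from top to bottom. The hypotension column is not. Outcomes {12} words one endpoint as a number of patients and the other as a number of events, so the count appears to be meant.

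**2. What the choice of test costs**

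The plan states no figure for this comparison, so there is none to reproduce. From the document: 60 patients allocated 1:1, hence 60/2 = 30 per arm. Assumed, because the document does not give them:

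- control rate r between 0.05 and 1 event per hour
- true rate ratio of 2
- observation time t uniform on 2 to 5 h
- between-patient variation in the rate as a gamma factor with mean 1 and variance 0.6

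For a patient observed t hours at group rate r, the probability of at least one event is

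1 − (1 + 0.6·r·t)^(−1/0.6).

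Averaged over t from 2 to 5 h, this gives the two any-event columns below. The control column uses r and the intervention column uses 2r. The power columns come from simulation at the two-sided 5% level.

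| Control rate per hour | Any event, control | Any event, intervention | Fisher, any/none | Mann–Whitney, events per hour |
|---|---|---|---|---|
| 0.05 | 15% | 27% | 11% | 19% |
| 0.1 | 27% | 44% | 17% | 30% |
| 0.2 | 44% | 63% | 23% | 44% |
| 0.5 | 69% | 84% | 19% | 65% |
| 1 | 84% | 93% | 9% | 75% |

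A repeat with 3,000 runs per rate gave 24% and 47% at 0.2 per hour, and moved the other power figures by no more than about 2 points. With no true difference, Fisher's test rejected in about 2–3% of runs and Mann–Whitney in about 5%, so part of the gap comes from the conservatism of Fisher's test.

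Fisher's power falls at high rates because most patients in both arms already have an event (84% against 93% in the last row). The difference then lies in how many events they have, which any/none cannot see.

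**3. A second set of assumptions**

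With negative binomial counts (dispersion 1.5), equal observation time, 30 per arm and mean counts of 1 v 2, 2 v 4 and 3 v 6, Fisher on any/none had about 22%, 18% and 10% power. Mann–Whitney on the counts had about 54%, 64% and 70%. The direction is the same.

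**The case against.** **Other endpoints cover the same harm.** The time-weighted average of hypotension is also planned. It reflects depth, duration and observed time, and as a continuous measure it falls under the t-test or Mann–Whitney rule. Vasopressor and fluid requirements are further hemodynamic endpoints. This stands. A reader might infer that the trial would miss its main safety signal, but the document names no such signal and does not rest hypotension on this one test.

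**Fisher's test need not mean any/none.** It extends to larger tables, for example 0, 1, 2, or 3 or more events per patient. That is true, so neither any/none nor pooling events across patients as if independent is forced. Such a table would still conflict with Table 1, ignore the order of the categories and ignore observation time.

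**The power figures depend on assumed rates.** They do. When events are rare both tests are weak, and changing the test does not rescue the endpoint. The simulation also holds the doubled rate constant throughout, whereas {11b} discontinues the intervention when hypotension requires treatment. The figures show a direction and a range, not a forecast.

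**An article may leave detail to the full protocol.** It may. Here, though, the article names the endpoint, the summary and the test, and they disagree.

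**The area formula.** A reader might also infer that the time-weighted average is computed wrongly, because the area is "calculated by summing the difference between MAP and the threshold, multiplied by the duration of the event". If readings are summed first and the sum is then multiplied by the whole duration, 60 mmHg for 5 minutes read every minute gives (5 × 5) × 5 = 125 mmHg·min instead of 5 × 5 × 1 = 25. The document does not support that as a finding. It calls the quantity an area under the threshold, the clause reads naturally as a sum of difference times duration, and no sampling interval is given.

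**Conclusion.** The contradiction holds: {20a} assigns a test for categorical data to an endpoint that Outcomes {12} and Table 1 treat as a per-patient number. This does not depend on any assumption.

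The loss from following {20a} with an any/none split does depend on assumptions. With control rates of 0.05 to 1 per hour, a rate ratio of 2 and 30 per arm, power is about 9–24% with Fisher's test and about 19–75% with Mann–Whitney on events per hour. The difference runs from about 8 points (19 − 11) at the lowest rate to about 66 points (75 − 9) at the highest.

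The point should be corrected, but its reach is limited to one secondary endpoint. The driving-pressure analysis and the 54 patients raised to 60 are untouched. The area formula merits at most a clearer wording and is not a demonstrated error.

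**What to change.** In {20a}, remove hypotension events from the Fisher sentence and keep that test for patients requiring supplemental oxygen, as Table 1 has it. Add one sentence: the number of hypotension events divided by observed anaesthesia time is calculated for each patient in events per hour, summarised by median and IQR, and compared between groups with the Mann–Whitney test. Naming the test directly avoids leaving it to the normality check. If an effect size is wanted, a rate ratio with confidence interval from a count model with log observed time as offset can be added, but it is not needed to resolve the contradiction.

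If the investigators do want a yes/no endpoint, they should define it in Outcomes {12}, amend the Table 1 footnote, and accept the lower power.

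As a wording clarification only, the area can be written as the sum, over readings below 65 mmHg, of (65 − MAP) × sampling interval.

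The cost is a sentence or two. The event data and monitor exports are already planned under {18a} and {19}. The drawback is that rates from short procedures are less stable than those from long ones.

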### Interim analyses {21b}

Not applicable, there will be no interim analyses.

### Methods for additional analyses (e.g., subgroup analyses) {20b}

Not applicable, further analyses are not planned.

### Methods in analysis to handle protocol non-adherence and any statistical methods to handle missing data {20c}

If the protocol could not be completely adhered to, or individual data is missing, a drop-out rate of 10% was considered in the sample size calculation. A per-protocol analysis will be performed with respect to the study intervention (PEEP setting). Data sets will only be excluded from the per-protocol analysis if the study intervention (PEEP setting) was not performed, or if the primary endpoint (ΔP) cannot be evaluated. For all other endpoints, if there are missing values, the number of missing values will be reported in the manuscript and analyses will be performed as planned.

### Plans to give access to the full protocol, participant-level data, and statistical code {31c}

Datasets containing anonymized patient data will be made accessible upon reasonable request to the corresponding author, in compliance with European data protection regulations (GDPR).

## Oversight and monitoring

### Composition of the coordinating centre and trial steering committee {5d}

The principal investigator is responsible for the monitoring of the study process. The study team consists of the principal investigator, a deputy investigator, and several sub-investigators and two study nurses. The group meets once every 2 weeks to discuss different issues and monitor the progress of the trial. The progression of the study, the presence of informed consent, review of the adherence to the study protocol, and verification of accuracy and completeness of the data will be checked by the principal investigator, the deputy investigator, and the two study nurses.

### Composition of the data monitoring committee, its role and reporting structure {21a}

This single-center pilot study is not powered to investigate patient-centered outcome parameters. We expect minimal risk from the study intervention. Therefore, no interim analyses are planned or will be performed, and a data monitoring committee has not been organized for this study.

### Adverse event reporting and harms {22}

Adverse events and other unintended effects of the trial will be collected, assessed, and immediately reported to the principal investigator. Potential harms and complications encompass instances of hypotension or hemodynamic instability necessitating intervention, as well as occurrences such as barotrauma, dislocation of the endotracheal tube, or peripheral oxygen saturation dropping below 92%. However, monitoring of patients will be conducted throughout their participation in the study, with treatment provided for any complications that arise. Incidences will be electronically recorded according to the study protocol and subsequently reported in the “Results” section.

### Frequency and plans for auditing trial conduct {23}

Not applicable, an auditing trail conduct is not required.

### Plans for communicating important protocol amendments to relevant parties (e.g., trial participants, ethical committees) {25}

Any changes in protocol will be submitted to the local ethics committee for approval, all changes will be communicated to the study team via email and during the regular study group meetings. The trial record on DRKS will be updated accordingly.

### Dissemination plans {31a}

Once the study has been completed, the results will be published in a peer-reviewed scientific journal and presented on national and international conferences for anaesthesiology and intensive care medicine.

## Discussion

This study aims to evaluate whether intraoperative PEEP adjustment according to BMI is safe, reduces driving pressure by increasing respiratory system compliance, and prevents loss of lung aeration as assessed by lung ultrasound in comparison to a standardized PEEP setting of 5 mbar.

Induction of general anesthesia and the subsequent loss of spontaneous respiration result in decisive changes in lung physiology, leading to atelectasis, reduced gas exchange, and reduced end-expiratory lung volume. These effects are partly dependent on body weight and might be more pronounced in obese patients, indicating the need for individualized ventilation strategies [9]. Nevertheless, the individualized approach must still be clinically feasible. Although the results may not be as ideal as with more elaborate methods of PEEP adjustment such as electrical impedance tomography or transpulmonary pressure measurement, a simple tool such as the rule of thumb PEEP = BMI/3 could represent a clinically feasible compromise between individualization and applicability.

Lung ultrasound has found widespread integration in clinical routine regarding the assessment of lung aeration in patients with dyspnea and acute respiratory failure [14] and is an established and readily available noninvasive method tool for the detection of postoperative pulmonary complications. Lung ultrasound allows early detection of changes in lung structure that are typical of PPCs, such as an increase in lung density due to atelectasis or effusions [15]. However, visualization of a single examination cannot be considered specific enough for diagnosis, thus it is deemed useful to perform an initial examination preoperatively before intubation and a follow-up examination postoperatively after termination of mechanical ventilation [12]. To establish longitudinal comparability and classify the severity of lung structural change, a standardized lung ultrasound scoring system should be applied [16]. The lung aeration score, based on the BLUE protocol [14], represents a validated score that has been successfully applied several times. Sonography is performed on spontaneously breathing patients in six regions per hemithorax, 0 to 3 points are assigned to each region according to the observed lung ultrasound pattern, and a sum is calculated. To evaluate the immediate postoperative outcome, oxygen saturation, required oxygen insufflation, and duration of stay in the recovery room will be analyzed as secondary outcome parameters. The length of stay in the recovery room will usually be half of the operating time and can be terminated as soon as the patient is hemodynamically and respiratory stable without further interventions.

To ensure reliable data collection and analysis, the team collecting the data was trained in the performance of lung ultrasound and the analysis team was trained in the use of the lung ultrasound score before the start of the study, using 20 sample patients. Therefore, to reduce examiner bias and prevent potential sources of error, acquisition and assessment of ultrasound images will always be performed by at least two different researchers. Lung ultrasound analyzers are blinded to group assignment and other clinical data.

Several previously conducted studies propose an association between high ΔP, high elastic-dynamic mechanical power (the product of ΔP, tidal volume, and respiratory rate) and unfavorable outcomes for patients with acute respiratory distress syndrome [17, 18]. For patients undergoing mechanical ventilation during general anesthesia, the available evidence suggests that a ventilation strategy that leads to a reduction in ΔP also reduces the risk of postoperative pulmonary complications [5]. For this reason, ΔP was chosen as primary endpoint in this trial. To further analyze the effect of PEEP adjustment according to BMI, respiratory system compliance, the different components of mechanical power (elastic-static, elastic-dynamic, resistive, total, tidal), intraoperative hemodynamics, postoperative oxygen requirements, and the number of intraoperative recruitment maneuvers required to maintain SpO_2_ > 90% with FiO_2_ < 60% will be recorded.

Available data suggest that 1 mbar increase in ΔP leads to a 16% relative risk increase for postoperative pulmonary complications (odds ratio for one unit increase of driving pressure 1.16) [5]. With an incidence of postoperative pulmonary complications around 5% in a mixed surgical population [1] and an assumed reduction of driving pressure by 1–2 mbar with PEEP adjusted according to BMI, a sample size of several thousand patients would be required to show a statistically significant reduction in postoperative pulmonary complications with our strategy. We therefore chose driving pressure as easy to measure and clinically relevant surrogate outcome parameter for our single-center trial assuming that a ventilation strategy that leads to a reduction in ΔP will ultimately reduce the risk of postoperative pulmonary complications in larger populations.

However, as this is the subject of the study, we cannot exclude with certainty that ΔP and the associated risk of postoperative pulmonary complications could also be increased with the ventilation strategy studied. Further limitations include that results may not be applicable to procedures with altered intrathoracic or intraabdominal pressures, such as laparoscopic or thoracic procedures or patient’s positions other than flat supine. Due to the study design the occurrence of PPCs could not be evaluated, this would have required a significantly higher number of patients. Thus, this aspect should be considered in further studies.

In conclusion, the study results will show whether an intraoperative ventilation strategy with PEEP adjustment based on BMI has the potential of reducing the risk for postoperative pulmonary complications as an easy-to-implement intervention that does not require lengthy ventilator maneuvers nor additional equipment.

## Trial status

The study protocol (version 1.1, date 31st January 2023) was approved by the ethics committee of the Christian-Albrechts-Universität Kiel, Germany, on 1st February 2023. Recruitment began on 3rd March 2023. Planned study completion date 30th September 2023.

## Data Availability

Following publication of the trial, datasets containing pseudonymized patient data will be made accessible upon reasonable request to the corresponding author.

## Abbreviations

ANOVA: Analysis of variance
AUC: Area under curve
BDSG: German Federal Data Protection Act
BMI: Body mass index
CRF: Case report form
EU-GDPR: European Union General Data Protection Regulation
PEEP: Positive end-expiratory pressure
*P*_insp_: Inspiratory pressure
PPC: Postoperative pulmonary complication
SpO_2_: Oxygen saturation
ΔP: Driving pressure
